## Abstract

**Background:**

Physical inactivity after surgery is an important risk factor for postoperative complications. Compared to conventional physiotherapy, activity-promoting video games are often more motivating and engaging for patients with physical impairments. This effect could be enhanced by immersive virtual reality (VR) applications that visually, aurally and haptically simulate a virtual environment and provide a more interactive experience. The use of VR-based fitness games in the early postoperative phase could contribute to improved mobilisation and have beneficial psychological effects. Currently, there is no data on the use of VR-based fitness games in the early postoperative period after colorectal surgery.

**Methods:**

This pilot trial features a single-centre, randomised, two-arm study design with a 1:1 allocation. Patients undergoing elective abdominal surgery for colorectal cancer or liver metastases of colorectal cancer will be recruited. Participants will be randomly assigned to an intervention group or a control group. Patients randomised to the intervention group will perform immersive virtual reality-based fitness exercises during their postoperative hospital stay. Feasibility and clinical outcomes will be assessed.

**Discussion:**

Early mobilisation after surgery is crucial for reducing many postoperative complications. VR-based interventions are easy to use and often inexpensive, especially compared to interventions that require more medical staff and equipment. VR-based interventions could serve as an alternative or complement to regular physiotherapy and enhance mobilisation after surgery. The proposed pilot study will be the first step to evaluate the feasibility of VR-based interventions in the perioperative period, with the aim of improving the postoperative rehabilitation of cancer patients.

**Trial registration:**

The trial has been registered in the German Clinical Trials Register (DRKS) Nr. DRKS00024888, on April 13, 2021, WHO Universal Trial Number (UTN) U1111-1261–5968.

**Supplementary Information:**

The online version contains supplementary material available at 10.1186/s40814-022-01213-x.

## Background

### Early postoperative rehabilitation

Restoring a patient’s physical fitness in the early postoperative period is of particular importance to reduce the risk of poor functional outcomes and complications such as respiratory tract infections and venous thromboembolism [1–3]. In most solid tumour diseases, surgical resection is the most important component of curative cancer therapy. Cancer patients often suffer from fatigue, decreased strength, pain, insomnia and psychosocial stress [4–10]. Surgery can further reduce a patient's fitness and reduce the quality of life.

Prolonged bed rest after the surgery is an important risk factor for postoperative complications and morbidity. Therefore, early mobilisation after surgery is strongly recommended by the Enhanced Recovery after Surgery (ERAS®) Society for most tumour entities [3, 11, 12]. In general, mobilisation of a patient includes activities such as sitting, standing and walking or passive exercises, which are started on the day of surgery and aim to reduce muscular and cardiovascular deterioration and prevent complications due to immobility. Physiotherapy in the early postoperative period plays an important role in achieving this goal.

Lack of staff and mobilisation support have been identified as causes of inadequate physiotherapy and mobilisation in patients undergoing abdominal surgery [13–15]. An Australian study showed that the durations of upright mobilisation were 3.0, 7.6, 13.2 and 34.4 in the first 4 days after upper abdominal surgery [13]. These figures differ greatly from the ERAS® recommendations [3, 12]. Patients undergoing major abdominal surgery require intensive mobilisation support as most of these patients are dependent on assistance in the first few days after surgery, and the need for support is likely to increase in the future as the general surgery population ages [13, 15]. Providing adequate physiotherapy in this patient group is particularly time-consuming and requires a significant amount of staff.

In addition, patient-related factors such as fatigue and non-compliance can result in the amount of exercise performed being significantly less than the amount of physiotherapy provided [8, 10, 16].

Activity-promoting video games are a subset of video games that have gained popularity over the last 15 years. In these games, the player must engage in various forms of physical activity or sports. While playing, energy consumption and heart rate increase in a similar way to physical activity of similar intensity [17, 18].

Although these games were developed for mass entertainment, they have attracted research interest because of their potential applications in the prevention and rehabilitation of a wide variety of diseases [17, 19–23]. In a rehabilitation or exercise setting, fitness games have the advantage over conventional rehabilitation and fitness exercises that they are actual games that evoke fun and enjoyment, which can increase motivation and compliance [24, 25]. Therefore, the use of VR-based fitness games for early postoperative rehabilitation could have additional positive effects on psychological well-being. Compared to conventional physiotherapy, fitness games are in many cases at least as effective and often more motivating and engaging for patients with physical impairments [26].

### Virtual reality

Virtual reality (VR) is an immersive and interactive technology that visually, aurally and haptically simulates a virtual environment and creates a sense of presence in that environment [27–29]. VR is being studied in various clinical settings and has attracted much attention as a low-cost and effective intervention, particularly in psychiatry [30].

The use of VR-based fitness games in the early postoperative phase could contribute to an improved mobilisation of patients and thus reduce the risk of postoperative complications. The improvement in mobilisation could be due to improved compliance and increased motivation, but also because after instruction and successful learning of the game, patients could perform exercises independently, thus reducing the need for staff. This could increase the daily duration of mobilisation. Accelerated postoperative rehabilitation could also have a positive impact on the length of stay. In addition, VR-based fitness games could have a positive effect on the well-being and quality of life of patients, as they can create fun and enjoyment, as well as a brief distraction from current worries, anxieties and the hospital environment.

### Rationale for a pilot trial

Currently, there are no data on the use of VR-based fitness games in the early postoperative period after colorectal surgery. There are no data available to estimate the effect size and thus enable a high-quality sample size calculation. Therefore, this pilot study aims to investigate the clinical and feasibility endpoints of the proposed intervention. Our aim is to assess, whether the design and protocol used will prove effective in terms of patient recruitment, patient compliance and patient acceptance of the intervention, and whether the intervention will have an impact on quality of life, general health, sleep, patient satisfaction, length of stay and complication rates.

## Methods

### Trial design and study population

This pilot trial features a single-centre, randomised, two-arm study design with a 1:1 allocation. The flowchart of the study design is shown in Fig. 1. Patients undergoing elective abdominal surgery for colorectal cancer or liver metastases of colorectal cancer will be recruited. Participants will be randomized to the intervention group or a control group that receives the standard treatment. Patients randomized to the intervention group will conduct virtual reality-based fitness exercises. This trial is conducted at the department of general-, visceral- and transplantation surgery at the University Hospital Augsburg.

**Fig. 1 Fig1:**
[figure not shown]
Trial flow chart

### Informed consent

All patients must provide written informed consent prior to participation. Patients who are unable to give consent, patients under legal guardianship and patients participating in another intervention study that has a potential impact on the endpoint of this study will be excluded from participation.

### Outcomes

#### Feasibility outcomes

The participation rate is the proportion of participants who meet the inclusion criteria and agree to participate in the study. The recruitment rate is the number of participants recruited per month. The retention rate is the number of participants who completed the total number of planned interventions.Proportion of interventions carried out in relation to planned interventions for each participant.Compliance with the intervention is measured as the percentage VR sessions started compared to the number of sessions offered.Rate of discontinued interventions and reasons for discontinuation.Compliance with the questionnaire completion is measured as the proportion of questionnaires completed by the set deadlines.Number of deviations from the study protocol (e.g. interventions not carried out or carried out differently than described in the study protocol, questionnaires not handed out or not completed) and reason for deviation from the study protocol (patient-related, staff-related, organisational).

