#### Clinical outcomes

Difference in health status assessed with the EQ-5D-5L health questionnaire [31] preoperatively, 7 days after surgery and 30 days after surgery.Difference in the number and severity of postoperative complications between the study groups the Clavien-Dindo classification and *Comprehensive Complication Index*® (CCI) [32, 33]Difference in length of hospital stay between the two study groups.Difference in psychosocial distress preoperatively, at 7 days and at 30 days, assessed with the NCCN Distress Thermometer [34].Difference in patient satisfaction at discharge assessed with the EORTC IN-PATSAT 32 [35].

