#### Control group

Patients in the control group receive the in-house physiotherapy standard.

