#### Secondary exclusion from the VR group

For patients who develop postoperative delirium, the intervention will be paused until the patients are consistently symptom-free and fully orientated for 24 h without drug delirium therapy. Patients with a reduced vigilance will not receive the VR fitness intervention as long as vigilance reduction persists. The VR fitness intervention will be paused while a participant is physically unable to sit in bed or at the side of the bed for 30 min. A new diagnosis of any of the conditions listed under the exclusion criteria will result in exclusion from the intervention group. New onset and continued use of any of the medications listed under the exclusion criteria will result in exclusion from the VR fitness group.

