### Sample size calculation

The feasibility study is being carried out with the aim to investigate the clinical and feasibility endpoints of the proposed intervention. Since there is no existing data to enable precise sample size calculations, we adhered to recommendations for sample size calculations in pilot trials. The current postoperative mean length of stay in our own patient population is approx. Thirteen days with a standard deviation of approx. 9.5. A targeted reduction in the length of stay by 2 days would result in a standardized effect size of 0.21. Whitehead et al. recommend a case number of *n* = 28 per group for pilot studies with a standardized effect size of 0.2 and a later planned study with a power of 90% [39]. In order to account for dropouts, e.g. due to non-completed questionnaires or study exclusions, 3 additional patients per group will be recruited. This results in a total number of 62 patients (31 per group).

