In terms of feasibility, we aim to achieve a minimum participation rate of 70% and a minimum compliance rate of 80% in terms of the completion of questionnaires and participation in the VR sessions offered. Trial participation rates and participation in VR sessions will be analysed during the study. If necessary, the reasons for low attendance rates are analysed and strategies to improve recruitment and participation in the VR sessions offered are discussed with team members.

Although this is a pilot study, we opted for a two-arm design as this provides data from a control, allowing a better understanding of the effect of the study intervention and a more accurate estimate of effect size. Even though randomisation is not a mandatory element of pilot trials we decided to use randomisation to further improve data quality and reduce selection bias. Even though the exercises could be performed by the patient without assistance, we chose to use supervision, to ensure that all exercises are performed correctly, to guarantee adherence to the protocol and to make sure that patients have no problems with the handling of the VR headset. Depending on the results, supervision could be omitted in future trials, if patients are adequately introduced to the system. This could provide an even greater degree of flexibility. The trial intervention could be performed after any abdominal surgery, but we decided to focus on colorectal cancer patients as colorectal cancer surgery is a common procedure and we wanted to ensure a relatively homogeneous patient population.

The proposed pilot study will be the first step to evaluate the feasibility of VR-based interventions in the perioperative period, with the aim of improving the postoperative rehabilitation of cancer patients.

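### The retention rate is defined as completing every planned VR session, so it does not show who stayed in the trial and has no value for the control arm

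*Protocol article*

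**What the plan says.** The protocol article defines the measure in one sentence under Feasibility outcomes: "The retention rate is the number of participants who completed the total number of planned interventions". No other section defines retention.

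The same list has two further measures of session delivery. One is "Proportion of interventions carried out in relation to planned interventions for each participant"; the other is the share of offered VR sessions that were started. It also has a questionnaire measure: "Compliance with the questionnaire completion is measured as the proportion of questionnaires completed by the set deadlines".

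The VR section offers one session per weekday until discharge, so the number planned is not fixed. For the other arm, "Patients in the control group receive the in-house physiotherapy standard". Health status and distress are assessed at baseline, day 7 and day 30 ("preoperatively, 7 days after surgery and 30 days after surgery" for the EQ-5D-5L).

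The Sample size calculation sets the dropout allowance: "In order to account for dropouts, e.g. due to non-completed questionnaires or study exclusions, 3 additional patients per group will be recruited". The Discussion sets a participation target of 70% and "a minimum compliance rate of 80% in terms of the completion of questionnaires and participation in the VR sessions offered". It sets no target for retention.

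**The concern.** A reader of a pilot report takes a retention rate to mean the share of randomised participants still in the trial at the end of follow-up, usually by arm. The definition here counts something else, and it can err in both directions. A patient who declines one session and is followed to day 30 is not retained. A patient who completes every session until discharge and then cannot be reached at day 30 is retained.

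The measure also cannot be compared between arms, because controls have no VR sessions to complete. It is worded as a count without a denominator. Because the number of planned sessions grows with length of stay, a longer stay gives more chances to fail it.

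At stake is the reading of one feasibility result. A low figure could mean that patients left the trial, or only that they skipped a session. The later study for which this pilot was sized needs the first kind of figure, by arm.

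**Working it through.** **1. The plan's own figures.** From the Sample size calculation: 2 / 9.5 = 0.21; 28 + 3 = 31 per group; 2 × 31 = 62. All match. The allowance implies 3/31 = 9.7% dropout per arm, so 28/31 = 90.3% remaining.

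**2. What the definition counts.**

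| Patient | Still in trial at day 30 | Retained as defined |
|---|---|---|
| VR, one session missed, day-30 data present | yes | no |
| VR, every session done, lost before day 30 | no | yes |
| Control, day-30 data present | yes | no value |
| Control, lost before day 30 | no | no value |

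Reading physiotherapy as the planned intervention does not rescue the control rows. Both arms receive it, its duration depends on the patient's condition, and the Physiotherapy section ends it once mobility and breathing criteria are met. There is no set total to complete.

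**3. Illustration of the gap.** Suppose all 31 VR patients remain to day 30, so true retention is 100%. Inputs:
- Mean stay 13 days, SD 9.5 (Sample size calculation).
- Weekday sessions at the mean stay: 13 × 5/7 = 9.3, about 9.
- Completion of 80% per session. This is an assumption borrowed from the Discussion's target, which concerns participation in sessions offered, and compliance is measured as sessions started, not completed.

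*Independent misses, everyone at the mean stay.* The share completing all sessions is p^m.

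| Per-session completion p | Sessions m | p^m | Of 31 |
|---|---|---|---|
| 0.80 | 5 | 0.328 | 10.2 |
| 0.80 | 9 | 0.134 | 4.2 |
| 0.80 | 11 | 0.086 | 2.7 |
| 0.90 | 9 | 0.387 | 12.0 |
| 0.95 | 9 | 0.630 | 19.5 |

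The first three rows show the dependence on stay: the same behaviour per session gives 33% with 5 sessions and 9% with 11.

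*Independent misses, stay varying between patients.* Since 0.8^N is convex in N, using the mean stay understates the average. Assume stay is gamma-distributed with mean 13 and SD 9.5, and sessions are 5/7 of days. Then the shape is (13/9.5)² = 1.87, the scale is (9.5²/13) × 5/7 = 4.96 sessions, and −ln 0.8 = 0.223. The mean of 0.8^N is (1 + 4.96 × 0.223)^−1.87 = 0.25, or 0.25 × 31, about 8 patients.

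*Other miss patterns, same 80%, equal session numbers.* If one fifth of patients account for all misses, 0.8 × 31 = 24.8 patients (80%) count as retained. If every patient misses at least one session, the figure is 0%.

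**4. Completion needed to show 28/31 under the stated definition.** With 9 sessions and independent misses, (28/31)^(1/9) = 0.989, so 98.9% of sessions would have to be completed even with nobody lost.

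**The case against.** The strongest reply is that the information is not lost. Questionnaire completion is reported and is not limited to the VR arm. Protocol deviations, including questionnaires not handed out or not completed, are recorded with reasons, as are discontinued interventions. Since day-30 assessments exist, participants with day-30 data can be counted per arm from what is already planned. The definition is also stated openly, and a measure confined to the VR arm is normal for intervention delivery. All of this stands, and it caps the importance of the point. It does not make the definition right: none of those items is defined as participants remaining per arm. Questionnaire compliance is a proportion of questionnaires, which could come out the same from a few patients lost entirely or from many each missing one form. Session adherence already has two measures, so this one adds a third under a misleading label.

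A reader might go further in four ways that the document does not support:
- That the pilot cannot inform dropout for the later study. It can, from the planned data.
- That retention was meant to test the allowance of 3 per group and fails to. No section gives it that job; the comparison is useful but is not one the plan promises.
- That 13% is the expected result. It depends on independent misses and on everyone having the mean stay.
- That medically paused days would count against patients. The article does not say how they are counted, and the full protocol may settle it.

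**Conclusion.** The point holds as a flaw in one outcome definition. As written, the retention rate is full VR-session completion: without a denominator, not applicable to controls, dependent on length of stay, and able to misclassify patients in both directions. That follows from the wording alone; reading planned interventions as VR sessions is an inference, but the only workable one.

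The size is illustrative. With nobody lost and 80% of sessions completed, the figure would be about 13% to 25% under independent misses and up to 80% under full clustering with equal session numbers, against the 90.3% implied by the allowance. The completion rate, the miss pattern and the distribution of stay are assumptions, so these figures show only that the two quantities can differ widely.

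The consequence is small. No feasibility target depends on retention, the sample size stays at 62, and no clinical comparison is affected. This is an improvement the sponsor could make, not a threat to the trial.

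**What to change.** Reword the sentence: retention is the number and percentage of randomised participants, in each arm, who are still in the trial with day-30 assessment data. The result can then be set beside the 28/31 (90.3%) that the dropout allowance implies. Report the number and percentage of VR patients who completed every planned session separately, under a name that says so, next to the existing proportion of sessions carried out.

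The cost is one reworded outcome definition and one renamed VR-arm result. The day-30 assessment already exists, so no visit or questionnaire is added, and the intervention, sample size and targets stay as they are.

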#### Clinical outcomes

Difference in health status assessed with the EQ-5D-5L health questionnaire [31] preoperatively, 7 days after surgery and 30 days after surgery.Difference in the number and severity of postoperative complications between the study groups the Clavien-Dindo classification and *Comprehensive Complication Index*® (CCI) [32, 33]Difference in length of hospital stay between the two study groups.Difference in psychosocial distress preoperatively, at 7 days and at 30 days, assessed with the NCCN Distress Thermometer [34].Difference in patient satisfaction at discharge assessed with the EORTC IN-PATSAT 32 [35].

### Interventions

#### Virtual reality (VR) fitness group

On weekdays, each participant in the VR Fitness Group is offered one VR-based activity-promoting fitness session using an immersive virtual reality fitness game until discharge with a maximum duration of 30 min. The sessions will be held in addition to the in-house physiotherapy standard that all patients receive after surgery. Heart rate and blood pressure are measured before each session and 10 min after the session begins to ensure an optimal heart rate for moderate-intensity exercise and to avoid fatigue.

All VR sessions are conducted in a seated position, either with the patient in bed or with the patient on the edge of the bed depending on the patient’s health and preference.

The first training session is conducted entirely under observation by a member of staff or a doctoral student from Augsburg University Hospital. For all subsequent training sessions, the first 10 min are performed under supervision. Participants who are able to continue their sessions on their own or do not require additional support are allowed to continue training on their own after the first 10 min until the end of the session.

The VR headset streams wirelessly to an external device during the first session to monitor the correct execution of the exercises and to guide the participants. This is to ensure that study participants understand the games and perform the exercises correctly. Study participants will also be guided in subsequent sessions as needed.

Only enjoyable content and no depiction of violence or brutal content will be used. Patients perform tasks such as rowing or cycling in a virtual environment as part of the training sessions. The performance of these activities requires the active movement of the upper body, arms, shoulders and hands.

The fitness sessions will be conducted using the Holofit app by Holodia (Holodia, Strasbourg, France) on an Oculus Quest 2 (Facebook Technologies LLC, Menlo Park, U.S.A) device with an Oculus controller in each hand.

